## 1.1 OBJECTIVES

**Primary objective:** To investigate whether a theoretically-informed telehealth intervention involving the HEARTS technical package and the use of an activity monitor to increase physical activity level is feasible to implement with individuals post-stroke.

**Secondary objective:** Estimate the parameters for carrying out a randomized clinical trial (RCT) considering the outcomes level of physical activity and number of individuals post-stroke who became physically active, systolic blood pressure (SBP) and diastolic blood pressure (DBP), cardiorespiratory fitness, self-efficacy for physical activity and health-related quality of life.

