## **2.5 Measurement of outcomes**

The measurement of primary and secondary outcomes will be carried out in NEUROLAB. Measurements will be carried out at the initial assessment (week 0), immediately after the end of the intervention program (week 12) and one month after the end of the intervention program (week 16). In the initial assessment (week 0), clinical and demographic data will be collected from all individuals for the purpose of verifying the eligibility criteria, identification and characterization of the sample. For this, a previously developed evaluation form will be used (APPENDIX 2). In weeks 12 and 16, a previously developed reassessment form similar to the evaluation form will be used, in addition to the addition of an assessment of the participant's satisfaction with the intervention carried out (APPENDIX 3). This collection will be carried out by a previously trained examiner, blinded to group allocation. All participants will be instructed not to comment on information about the training received.

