#### **2.5.2 Secondary outcomes: clinical measures**

Clinical outcomes will be evaluated to estimate the parameters for carrying out an RCT, including: level of physical activity and number of individuals post-stroke who became physically active, SBP and DBP, cardiorespiratory fitness, self-efficacy for physical activity and health-related quality of life.

The level of physical activity and the number of individuals post-stroke who became physically active will be measured with the HAP (Souza et al., 2006). The HAP is a questionnaire, applied in the form of an interview, consisting of 94 activities, each one graded hierarchically according to the metabolic equivalent required (Teixeira-Salmela et al., 2007, Souza et al., 2006). Activities include personal care, transportation,

home maintenance, social and leisure activities, and physical exercise. For each item, there are three possible answers: “still does the activity”, “stopped doing it” and “never did it” (Teixeira-Salmela et al., 2007, Souza et al., 2006). The maximum activity score (MAS) indicates the activity with the highest energy expenditure that the individual is capable of performing (Teixeira-Salmela et al., 2007, Souza et al., 2006). An AAS is obtained by subtracting from the maximum score the number of activities that the individual stopped performing and indicates the average level of typical metabolic equivalent (Teixeira-Salmela et al., 2007, Souza et al., 2006). Higher scores indicate better results (Souza et al., 2006). The level of physical activity will be operationalized by the AAS, in points (Souza et al., 2006). Another measure of the HAP is the “Activity Classification”, which provides an overall classification of the individual's activity level into “Inactive”, “Moderately active” and “Active”. The number of individuals who have become “Moderately Active” and “Active” will be identified. The HAP is an instrument already adapted to Portuguese-Brazil, which presents appropriate measurement properties for assessing the level of physical activity of individuals post-stroke (Teixeira-Salmela et al., 2007, Souza et al., 2006).

SBP and DBP will be operationalized as the average of the pressures obtained. These measurements will be obtained using the Tycos® aneroid sphygmomanometer (WelchAllyn Inc., NY, USA, Model DS-44) and the stethoscope (Litmann Classic II SE 3M®, USA).

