Cardiorespiratory fitness will be measured by HAP (Souza et al., 2006). One of the HAP measures is “Lifestyle Energy Consumption”, operationalized in  $\text{ml.kg}^{-1}.\text{min}^{-1}$  (Souza et al., 2006). The HAP is a valid instrument for estimating the cardiorespiratory fitness of individuals post-stroke (Brito et al., 2022).

Self-efficacy for physical activity will be operationalized considering the score obtained on the Self-Efficacy for Physical Activity Scale (Rech et al., 2011). No instrument was found that presents adequate measurement properties to assess self-efficacy for physical activity in individuals post-stroke. The scale presents 10 questions, divided into two sections (Rech et al., 2011). Each question must be answered as yes (1 point) or no (0 point) (Rech et al., 2011). Scores are computed with the sum of the answers to each question (Rech et al., 2011). The higher the value, the higher the self-efficacy for practicing physical activity (Rech et al., 2011). Rech et al. (2011) investigated the measurement properties of the scale and identified that it presents adequate validity,

internal consistency and reproducibility to assess self-efficacy for physical activity in Brazilian adults.

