## **2.6 Sample calculation**

As a feasibility study, no formal sample size calculation is performed (Billingham et al., 2013). Following the recommendation proposed by Julious (2005) for feasibility studies with parallel groups, the present study will present a sample size of 24 individuals, with 12 individuals in each group.

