## **2.8 Statistical Analysis**

All statistical analyzes will be carried out by an independent examiner, blinded to all procedures carried out in the study, including group allocation. Descriptive statistics will be calculated for all results. Effect sizes will be calculated to determine the magnitude of within- and between-group comparisons. All analyzes will be carried out using the SPSS 20.0 statistical program and  $\alpha=0.05$  will be considered, adjusted for multiple comparisons.

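### Section 2.8 attaches a multiplicity-adjusted significance level to clinical outcomes that serve only to estimate RCT parameters, in a sample of 12 per group not sized for testing

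*Protocol*

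**What the plan says.** Section 2.8 of the protocol plans three things. Descriptive statistics are to be produced for all results. On effect sizes it says "Effect sizes will be calculated to determine the magnitude of within- and between-group comparisons". Finally, for all analyses, an alpha of 0.05 "will be considered, adjusted for multiple comparisons". It names no test, no adjustment method and no family of comparisons.

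The purpose of the clinical outcomes is set elsewhere. In section 1.1 the primary objective is feasibility, and the secondary objective begins "Estimate the parameters for carrying out a randomized clinical trial (RCT"). Section 2.5.2 repeats this purpose and lists the outcomes: "level of physical activity and number of individuals post-stroke who became physically active, SBP and DBP, cardiorespiratory fitness, self-efficacy for physical activity", followed by health-related quality of life. That makes seven. Section 2.5 measures them at baseline, week 12 and week 16.

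On size, section 2.6 says "As a feasibility study, no formal sample size calculation is performed" and, citing a published recommendation for parallel-group feasibility studies, "the present study will present a sample size of 24 individuals, with 12 individuals in each group".

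**The concern.** The objectives and the sample size section describe an estimation study. The alpha clause in section 2.8 describes a testing study, because adjusting a significance level for multiple comparisons only does something when several hypotheses are each accepted or rejected. The two do not fit together, and the clause is the part that fits badly.

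Two misreadings are at stake. A non-significant between-group result, which is the likely outcome even if the monitor has a moderate effect, may be taken as evidence that it adds nothing. A significant one can arise only from a very large observed difference, which will tend to overstate a modest true effect. Neither reading gives the next trial what section 1.1 promises, namely usable parameters with a statement of how well they are known.

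Small to moderate effects are the range of interest if the monitor's added benefit is modest. By section 2.4 both groups receive the HEARTS package and differ only in the activity monitor. The protocol states no expected effect, so this is an assumption.

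**Working it through.** **The plan's own figure.** 2 × 12 = 24 agrees with section 2.6. No power, target difference or SD is stated, so nothing further can be reproduced.

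**Inputs.**
- From the protocol: n = 12 per group (2.6); alpha = 0.05 with adjustment (2.8); seven clinical outcomes (2.5.2); two post-baseline visits (2.5), so up to 7 × 2 = 14 between-group comparisons.
- Assumed: two-sided tests, a two-sample t-test for continuous outcomes, no dropout, and Bonferroni with m = 1, 7 or 14.

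**Step 1: critical values.** With 2 × 12 − 2 = 22 degrees of freedom, c = t(1 − 0.05/(2m); 22), which gives 2.074 for m = 1, 2.965 for m = 7 and 3.262 for m = 14.

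**Step 2: smallest observed d that can be significant.** d_min = c × √(2/12) = c × 0.408:
- m = 1: 2.074 × 0.408 = 0.85
- m = 7: 2.965 × 0.408 = 1.21
- m = 14: 3.262 × 0.408 = 1.33

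**Step 3: power.** Power = P(T > c), where T is noncentral t with 22 df and noncentrality d × √(12/2) = 2.449 × d. At d = 0.5 the noncentrality is 1.22.

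| Comparisons (m) | alpha per test | d = 0.2 | d = 0.5 | d = 0.8 | d = 1.2 | d for 80% power |
|---|---|---|---|---|---|---|
| 1 | 0.05 | 7% | 22% | 47% | 80% | 1.20 |
| 7 | 0.0071 | 1% | 6% | 19% | 50% | 1.57 |
| 14 | 0.0036 | 1% | 4% | 13% | 40% | 1.70 |

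For the number who became active, an assumed 20% versus 40% gives power of 18% unadjusted and 5% with m = 7. With 10 per group remaining (assumed), power at d = 0.5 is 18% unadjusted and 5% with m = 7.

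**Step 4: precision of the observed effect size.** Suppose the observed d is 0.5, so t = 0.5 × 2.449 = 1.225. The noncentrality values that place this t at the 97.5th and 2.5th percentiles are −0.781 and 3.204. Dividing by 2.449 gives a 95% CI for d of −0.32 to 1.31. For a raw mean difference, the 95% CI half-width is 2.074 × 0.408 = 0.85 SD.

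**Step 5: precision of the SD.** The 95% limits of the pooled SD, relative to its estimate, are √(22/36.78) = 0.77 and √(22/10.98) = 1.42. Required sample size scales with the square of the SD for a fixed target difference, so these limits correspond to factors of about 0.77² = 0.60 and 1.415² = 2.00. The SD is the more useful planning quantity, but it too must be given with its interval.

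**The case against.** Several points on the other side are sound.

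- **Variability.** A reader might infer that the plan reports effect sizes with no measure of spread. The text does not support this. Section 2.8 plans descriptive statistics for all results, which ordinarily include the SD, and a standardised effect size cannot be computed without one.
- **Intervals.** Section 2.8 neither promises nor excludes confidence intervals, and a statistical analysis plan not shown here may supply them. Their absence alone is not a finding.
- **Sizing the RCT.** A reader might infer that the next trial will be sized on the observed effect. No section says so. It is a risk that follows from pairing effect sizes with a parameter-estimation aim, not a stated intention.
- **Power.** It would be too strong to say that tests here have almost no power. Unadjusted between-group power reaches 80% at d = 1.2. The planned within-group comparisons also do better: a paired test with 12 has 71% power at a standardised change of 0.8, falling to 36% with m = 7. Bonferroni over 14 is a severe case. A milder method, a smaller family, or an allowance for the correlation among outcomes taken from the same HAP interview would lose less. The unadjusted row bounds this from above, and it is still only 47% at d = 0.8.
- **Consequence.** The primary outcomes are feasibility measures, and no stated decision depends on a p-value for a clinical outcome.

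These points narrow the concern without removing it. The alpha clause is stated and applies to all analyses. An analysis plan could add detail to it, but the clause would still conflict with the objectives.

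**Conclusion.** The concern holds as a mismatch between a stated rule and a stated purpose. Section 2.8 puts a multiplicity-adjusted significance level on outcomes that sections 1.1 and 2.5.2 assign to estimation, in a sample that section 2.6 does not size for tests. Between-group tests would miss a moderate effect roughly four times in five without adjustment (22% power at d = 0.5). With the assumed adjustment they would miss it about 19 times in 20 (4% to 6%).

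The unadjusted figures rest on a two-sided t-test with full retention. The adjusted ones also rest on Bonferroni and on counts of 7 or 14, which the protocol does not specify. The choice of 12 per group is not criticised, and the feasibility objective is unaffected. The point is worth correcting because the correction is cheap, but it does not undermine the study.

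**What to change.** Replace the alpha clause in section 2.8 with an estimation statement along these lines:

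- Clinical outcomes are reported as baseline-adjusted between-group differences with 95% confidence intervals. The number who became active is reported as a proportion per group with its interval, since section 2.2 admits only people classed as inactive.
- The pooled SD and the baseline-to-follow-up correlation, each with a confidence interval, are named as the parameters carried forward to the RCT.
- Any p-value is labelled exploratory and is not used to judge efficacy.
- The observed effect size is not used alone to size the RCT.

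The cost is a few sentences. No participant, visit or measurement changes. The sponsor gives up confirmatory p-values on clinical outcomes, which carry little information at this size.
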